#### Implementation phase (October 2019–September 2020)

During this phase, additional measures have been introduced:

Implementation of wound protectors during colorectal surgery.Colorectal operations were only performed with the support of an experienced consultant surgeon.

#### Post-implementation phase (January 2021 – December 2021)

During this phase, additional measures are being implemented.

Close monitoring of blood glucose. During the stay in the recovery room and for 48 hours post-operative, blood glucose is monitored closely. Moreover, if blood glucose is higher than 9 mmol/l, the patient will be treated with insulin. This measure is applied to diabetic as well as to non-diabetic-patients.The measures of warming are intensified. First of all, during the operation and during the stay in the recovery room, patients will be placed on warming mattresses. Moreover, a warming towel will be placed on the operating field directly after the operation.The patients will be asked to take a shower the night before surgery. In case of an emergency operation, patients will be asked to wash the axilla, trunk, genitalia, groins and umbilicus.

The primary endpoint of this study is occurrence of SSI within 30 days after surgery. Evaluation of risk factors for SSI will be secondary endpoints. In ***Table 1***, the patient-associated risk factors and procedure-associated risk factors assessed in our study protocol are listed.

**Table 1 T1:** Questionnaire for SSI Risk factors.

PATIENT ASSOCIATED RISK FACTORS	PROCEDURE ASSOCIATED RISK FACTORS

Age	Date of the operation?

Sex	Duration auf the operation (min)

Diagnosis	What kind of operation was performed?

Weight	Which technique of surgery was done (open, laparoscopic, robotic)?

Fat tissue measured in CT scan	Which type of stoma was inserted?

Height	

BMI	

Diabetes and what kind of diabetes	

HbA1c	

Alcoholism	

Immune-deficiency diseases and which type of disease exactly	

Smoking	

Immunosupressive drugs and which ones	

Chemotherapy	

Radiotherapy	

COPD	

pAVK	

Renal insufficience	

Length of hospitalization	

Pre-Albumin	

ASA Score	

Contamination Class of wounds	

Moreover, we measure pre-albumin levels to determine the nutritional status. We assess whether immune-modulatory supplements like Oral Impact^®^ have been given before surgery. We include the ASA (American Society of Anesthesiologists) score in our data to define the general health status of the patient. Furthermore, we classify the grade of contamination of the wound prior to surgery.

After the operation, we assess compliance by evaluating whether the nine measures of our colorectal bundle of care were performed as planned. If SSIs occur, we classify them and treat them according to the guidelines. Patients will be followed for the occurrence of SSIs within 30 days after surgery by means of a telephone survey. These telephone surveys have also been done during the pre-implementation and implementation phase. Our goal-directed questions enable patients to recognize symptoms suspicious of a SSI at home. Criteria for wound infection comprise redness and pain around the wound, drainage from cloudy fluid, fever, wound dehiscence, etc. If patients report suspicion of SSI, we strongly advise them to present themselves at our outpatient clinic or at the family doctor for evaluation and treatment.

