**Highlights::**

## Background

SSIs are a common problem in the healthcare system [1]. They lead to an increased mortality and morbidity rate. Apart from the negative impact on patients, SSIs cause high healthcare costs due to prolonged hospital stay and readmission of patients. Colorectal surgery, in particular, is associated with a high infection rate ranging from 15% to 30% [2,3].

In order to understand the causes of SSIs, risk factors have to be evaluated. Intrinsic and extrinsic factors have previously been defined [4]. Intrinsic risk factors are patient-associated and can be subclassified in modifiable and non-modifiable features. Modifiable intrinsic risk factors include diabetes, alcoholism, smoking status, obesity and preoperative albumin level. Examples of non-modifiable risk factors include age and recent radiotherapy. Extrinsic risk factors are procedure-related and involve emergency surgeries or facility risk factors. There are several strategies to prevent SSIs. The biggest impact has been found in the combination of different measures into a bundle of care [5,2,6].

The Cantonal Hospital Lucerne (LUKS) is an 870-bed public acute care teaching hospital serving a population of about 500.000 people in central Switzerland. From October 2016 till September 2017 the rate of SSIs in colorectal surgery in LUKS was 18.1% whereas the average rate of SSIs in Switzerland was 13.7% during the same period of time [7]. These nationwide data were collected and analyzed by Swissnoso, an organization monitoring SSIs cross-disciplinary.

In order to reduce the SSIs at LUKS, we created a colorectal bundle containing 9 measures. These measures were based on a literature research and selected in cooperation with the Department of Hospital Infection Control.

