### Statistical methods

Data will be presented as absolute and relative frequencies for categorical variables and using descriptive statistics for continuous variables.

The primary endpoint, occurrence of SSI within 30 days after surgery, will be determined as a rate (number of patients experiencing SSI/number of patients undergoing colorectal surgery). The SSI rate will be determined together with a 95% confidence interval according to Clopper-Pearson.

The SSI rate will be compared to the SSI rates obtained for previous years (pre-implementation phase implementation phase) in an unadjusted manner as well as after adjustment for NNIS risk index. The NNIS risk index will be applied according to the methodology of Swissnoso and is based on ASA score, surgical wound classification and duration of surgery.

Potential risk factors of SSIs will be evaluated in an exploratory manner by measures of association and utilizing logistic regression models.

The sample size in this observational study is based on the expected number of patients undergoing colorectal surgery annually. With approx. 150 patients, the half-width of the 95% confidence interval for the SSI rate will not exceed 6.5% as long as the SSI rate is not greater than 18%.

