## Discussion

SSIs are a major challenge in patient care after colorectal surgery. A high number of SSIs leads to an increase in hospital length of stay, readmission rates, and healthcare costs [3]. Over the last years, several studies have shown that the combination of multiple SSI reduction measures into a bundle can significantly reduce SSI rates [5]. The impact of the individual measure and thus the “right” combination of a bundle of care for a single institution remains unclear [2].

The rate of SSIs is considered as quality factor for surgical care and thus we aimed to improve outcome quality with the implementation of a bundle of care in colorectal surgery at our institution. Since a variety of risk factors contribute to SSIs, it is widely believed that improvement cannot be achieved by one single action, even though each single action has been shown to reduce SSIs significantly in former studies. As a consequence, the implementation of a bundle of measures is necessary. Nevertheless the effectiveness and moreover the achievability of compliance and adherence to all these measures by a multidisciplinary team, is still under discussion. On the one hand, the positive effect of reduction of SSIs has been demonstrated in former studies [3]. On the other hand, some studies have shown that although every single action has a high level of evidence the bundle of care itself cannot reduce the rate of SSIs [22,23,24].

In our institution, an increasing number of SSIs in patients undergoing colorectal surgery could be observed over the last years. To improve patients` outcomes a colorectal bundle of care was gradually implemented over three years as a monocentric, prospective observational study.

To address and prevent malcompliance in a large multidisciplinary team repetitive instructions and trainings have been performed and for each action and team respectively a separate checklist was created. In addition, we plan meetings with the responsible team members on a monthly basis to update and raise awareness.

Several bundles with numerous separate actions have been described in literature. We have reflected our workflows and selected a comparatively high number of nine measures, which should be most effective in our setting to decrease the rate off SSIs. Regular information and instruction of all the involved teams and the rising of awareness towards this topic, can lead to behavioral changes contributing to a decrease of SSIs.

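### Table 1 lists length of hospitalization, not limited to the preoperative stay, as a risk factor for SSI, although the protocol itself says that SSI prolongs the stay

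*Protocol article*

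**What the plan says.** The protocol article, under Post-implementation phase, sets the outcome and the secondary aim: "The primary endpoint of this study is occurrence of SSI within 30 days after surgery", and "Evaluation of risk factors for SSI will be secondary endpoints". It introduces Table 1 by saying that there "the patient-associated risk factors and procedure-associated risk factors assessed in our study protocol are listed". The patient column of that table contains "Length of hospitalization". No start or end point is given, and nothing in the article limits the item to the preoperative stay or sets it apart as an outcome.

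Statistical methods gives the analysis: "Potential risk factors of SSIs will be evaluated in an exploratory manner by measures of association and utilizing logistic regression models".

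On the direction of effect, Background says that "SSIs cause high healthcare costs due to prolonged hospital stay and readmission of patients", and Discussion says: "A high number of SSIs leads to an increase in hospital length of stay, readmission rates, and healthcare costs".

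**The concern.** A risk factor has to be in place before the event that it is meant to explain. Unless it is limited to the days before surgery, a hospital stay runs on after the operation and therefore overlaps the 30-day window in which SSI is counted. By the protocol's own account, SSI lengthens it. The article thus names the same variable as a consequence of SSI in two places and as a risk factor for SSI in a third.

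Two things are at stake, both within the secondary analysis. First, length of stay could be reported as a risk factor for SSI when the association arises partly or wholly because infected patients stay longer. Second, if stay is placed in a model beside other candidates, it can take over part of the association that belongs to a genuine risk factor which also affects the stay.

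**Working it through.** **The plan's own figure.** The only planning figure in Statistical methods is the confidence-interval half-width of at most 6.5% for about 150 patients and an SSI rate up to 18%. With 150 × 0.18 = 27 events, the Clopper-Pearson limits are the beta quantiles B(0.025; 27, 124) = 12.2% and B(0.975; 28, 123) = 25.1%. Half the width is 6.44%, so the figure reproduces. It concerns the primary rate and does not bear on this point.

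**The passages side by side.**

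1. Table 1 and the sentence that introduces it make length of hospitalization one of the risk factors to be assessed.
2. Statistical methods assigns potential risk factors to association measures and logistic models of SSI.
3. Background and Discussion state that the effect runs from SSI to stay.
4. The outcome window is the 30 days after surgery, so a stay measured to discharge is complete only after any SSI that arose in hospital, and includes the days that it added.

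From 1 and 2, following the article as written means measuring the association between SSI and stay and reading it as information on risk. From 3 and 4, that association contains a component in the reverse direction. This holds for a single univariable measure as well as for a multivariable model.

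**Illustration of size.** The documents give no lengths of stay, so every stay-related value here is an assumption. Each simulated study has 150 patients and an SSI probability of 18%. Baseline stay follows a gamma distribution with mean 8 and SD 4 days and has no effect on SSI. Observed stay = baseline stay + d × (1 if SSI, otherwise 0). SSI is regressed on observed stay by logistic regression and tested at the two-sided 5% level, in 1,000 simulated studies per value of d.

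| Days added by SSI (d) | Stay significant | Median odds ratio per day |
|---|---|---|
| 0 | 5% | 1.00 |
| 2 | 61% | 1.12 |
| 4 | over 99% | 1.24 |
| 7 | 100% | 1.45 |

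With d = 0 the test keeps its nominal 5%. Everything above that is reverse causation.

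**Effect on another factor.** In a second assumed scenario, a genuine risk factor has an odds ratio of 1.8 per SD and also lengthens the stay: baseline stay is multiplied by exp(0.2) per SD. The logistic intercept is −1.6, and there are 600 simulated studies per value of d.

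| d | Median odds ratio, stay not in model | Median odds ratio, stay in model |
|---|---|---|
| 0 | 1.82 | 1.87 |
| 4 | 1.81 | 1.27 |
| 7 | 1.82 | 0.95 |

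The genuine factor is recovered without stay in the model. With stay included, it is weakened at d = 4 and lost at d = 7. With d = 0 there is almost no change, so the distortion comes from the days that SSI adds.

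**The case against.** The strongest case on the other side has five parts.

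- **Table 1 is a data-collection form, not a covariate list.** It also holds the operation date, the diagnosis, and weight, height and BMI together, which nobody would enter as they stand. Statistical methods names no covariates and does not refer to the table. This stands in part: a reader might infer that every Table 1 item will enter a multivariable model, and no sentence says so. But the text introducing the table calls its items the risk factors assessed, and that is enough for a univariable association to be expected.
- **The item is undefined.** Preoperative stay may have been meant. The article does not exclude that reading, but nothing in it supports it either, and it cannot be left to the analyst to guess.
- **The named hypotheses do not involve it.** Abstract, Background and Discussion name factors such as obesity, age, diabetes, alcoholism and smoking. This is correct, and it lowers the weight of the point. It does not remove the item from the table.
- **Not every SSI lengthens the stay.** The 30-day telephone survey also finds infections that appear after discharge. If the item means the index admission, these cannot have prolonged it. This stands. The share is not given. If, for example, half of the SSIs arose before discharge and each added 4 days, the average addition would be 0.5 × 4 = 2 days, and the illustration would weaken accordingly.
- **The analysis is exploratory.** That limits the weight of its conclusions but does not change the direction of the association. Background gives understanding the causes of SSI as the reason for evaluating risk factors, and a consequence of SSI cannot serve that purpose.

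**Conclusion.** The point holds in a conditional form. The article classifies length of hospitalization, with no restriction to the preoperative stay, as a risk factor for SSI, and states twice that SSI prolongs the stay. If it is evaluated as Statistical methods plans for potential risk factors, the result will at least partly reflect reverse causation, chiefly from SSIs that arise before discharge. If it enters a multivariable model, it can also distort the coefficients of factors that affect the stay.

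The size is not known from the documents. The simulated figures rest on assumed stays and assumed added days, and on the upper planning rate of 18%. They show what is possible, not what this study will find.

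Two stronger readings are not supported. One is that the secondary conclusions as a whole would be wrong, with the coefficients of age, ASA score or obesity sure to move toward or past zero. Univariable results for those factors do not depend on stay at all, and in a joint model the change depends on which variables enter and on how each relates to stay. The other is that the main result is compromised. The primary SSI rate, its Clopper-Pearson interval and the comparison adjusted for the NNIS risk index (ASA score, wound class, duration of surgery) do not use length of stay.

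The item should be corrected before the risk-factor analysis is run.

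**What to change.** Choose one of two changes and state it in the analysis plan.

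1. Take length of hospitalization out of the SSI risk-factor candidates and report it as an outcome, described by SSI status. State whether readmission days count.
2. If stay is of interest as an exposure, redefine the Table 1 item as preoperative stay: days = operation date − admission date.

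The two can be combined, with preoperative stay as a candidate and length of hospitalization as an outcome.

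The operation date is already in Table 1, so the only possible extra item is the admission date. No planning figure, sample size or primary analysis changes.

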### Patient population

All patients undergoing colorectal surgery from January 2021 until December 2021, fulfilling the inclusion criteria and having signed an informed consent form will be included in the study. According to our annual case load, we expect to enroll about 150 patients in the study. The data of the patients which are prospectively included in this study will be compared with the data analyzed by Swissnoso (October 2017–September 2018 and October 2018–September 2019). From 2017–2018 153 patients were included and 31 infections were detected (5 superficial, 8 deep and 18 involving the abdominal cavity).

From 2018–2019 after partial implementation of the colorectal bundle actions 126 were included and 15 infections occurred (2 superficial, 4 deep and 9 involving the abdominal cavity). Concerning the three time periods, data acquisition is retrospective for the first two periods and prospective for the final period.

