There are multiple studies assessing the different methods of hair removal prior to surgery [8], such as shaving, clipping and chemical depilation. Compared with shaving, clipping leads to a significant reduction of SSI [9]. During shaving, the skin experiences microscopic cuts which can lead to colonization of microorganisms and thereby increases susceptibility for post-operative wound infections. Therefore, our first action is to remove hair with a clipper.Surgery leads to a release of catabolic hormones as well as decrease in pancreatic beta-cell function, causing stress-induced hyperglycemia. Several studies have shown the association between hyperglycemia and elevated risk for SSI. Close glucose monitoring leads to a reduction of SSI, especially in non-diabetic patients [10]. A risk of hypoglycemia is described, but no serious adverse events occurred during treatment [11]. The second action is therefore the monitoring of blood glucose and the treatment with either insulin or glucose according to our scheme.The application of antibiotics in order to reduce SSI is well established [12]. Studies show that the optimal time window for surgical antimicrobial prophylaxis is 30–59 minutes prior to incision [13]. Accordingly, our third action is to apply an antibiotic prophylaxis within the time frame.Zanetti et al. could demonstrate that the redosing of prophylactic antibiotics during cardiac surgery can significantly reduce SSI [14]. Subsequently, the fourth action is to repeat the intravenous antibiotics if the operation lasts more than four hours.The fifth action focuses on optimal body temperature. Perioperative hypothermia leads to SSI [15,16]. The application of warming systems reduces infections in colorectal surgery [17]. If core temperature is below 35°C, additional warming tools are applied, such as warm intravenous fluid. There is limited data on adverse effects, such as thermal burns.The sixth action includes glove and instrument changes after finishing the anastomosis. Wearing the same gloves over a long period of time may cause microbiological contamination. Hence, in arthroplasty surgery, changing gloves was shown to significantly reduce SSI [18]. A change of instruments prevents a potential bacterial contamination of the abdominal cavity.The seventh action is the use of wound protectors. In laparoscopic as well as in open surgery, dual ring wound protectors lead to a reduction of SSIs [19]. Most likely, a barrier between surgical field and wound can decrease bacterial contamination [20]. Prevention of temperature loss of the wound leads to an improved blood perfusion and reduces SSI.The eight action concerns the surgeons’ experience. Colorectal operations are exclusively performed with the support of a well experienced consultant surgeon.Our ninth and last action focuses on preoperative showering. Torres et al. have shown that a shower, even with customary soap the night before surgery, can significantly reduce SSIs [21].

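### The only timing given for wound contamination grading is before surgery, which does not fit the surgical wound class that the NNIS adjustment needs

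*Protocol article*

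**What the plan says.** In the protocol article, the text after Table 1 (section on the post-implementation phase) describes what is recorded for each patient and ends: "Furthermore, we classify the grade of contamination of the wound prior to surgery". Table 1 lists the item as "Contamination Class of wounds" in the patient-associated column. No other wound-class item appears.

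The Statistical methods section plans to compare the 2021 SSI rate with earlier rates "in an unadjusted manner as well as after adjustment for NNIS risk index". On scoring, it says: "The NNIS risk index will be applied according to the methodology of Swissnoso and is based on ASA score, surgical wound classification and duration of" the operation. No other adjustment is named for this comparison.

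On the comparators, the Patient population section says the 2021 data "will be compared with the data analyzed by Swissnoso (October 2017–September 2018 and October 2018–September 2019", and that "data acquisition is retrospective for the first two periods and prospective for the final period".

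The account of the bundle gives this reason for one of its measures: "A change of instruments prevents a potential bacterial contamination of the abdominal cavity". The protocol therefore itself treats contamination during the operation as possible.

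**The concern.** The wound-class component of a surgical risk index should describe the operation that took place. Spillage is an event of the operation, and an unexpected perforation or peritonitis may be recognised only on opening. Emergency cases are eligible, so such findings are not remote. A grade settled before incision is a forecast from the planned procedure.

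This is a non-randomised comparison of calendar periods, and NNIS is its only named case-mix adjustment. If the wound-class component misses intraoperative contamination, the adjustment removes less confounding than intended. If it misses it in one period only, it adds a bias of its own. Wound class is also one of the risk factors studied as secondary endpoints, and its association with SSI would be diluted by high-risk patients placed in lower classes.

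**Working it through.** **1. Trace the NNIS inputs to the data collected.** The index needs three items, and each appears once in Table 1:

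- ASA score: listed as ASA Score. The text gives no particular timing.
- Duration of surgery: listed in minutes, and known only when the operation ends.
- Surgical wound classification: the contamination class. The only timing stated is before surgery.

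The contamination class is the only documented source for the third input. Because duration is needed too, the index cannot be computed before the operation is over, so early grading gains nothing.

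**2. Test both readings of the sentence.** The timing phrase may say when the grading is done, or which state of the wound is graded. The surrounding text favours the first: the preceding sentences record supplements given before surgery, and the next paragraph turns to what is assessed afterwards. On either reading, contamination arising in the operation is not counted.

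**3. Check the plan's own figure.** The only precision statement is: "With approx. 150 patients, the half-width of the 95% confidence interval for the SSI rate will not exceed 6.5" per cent, for an SSI rate up to 18%. With 27 events in 150 patients (18%), the Clopper-Pearson limits are 12.21% and 25.10%, and half their distance is 6.44 percentage points. The statement holds and does not involve wound class.

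**4. Illustrate the possible bias.** The documents give no wound-class distribution and no SSI risk by class, so every input here is an assumption:

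- no true difference between periods;
- SSI risk r0 = 0.12 without the wound-class point;
- odds ratio OR of 2 or 3 for the point;
- share c of patients who truly qualify for it, 10% to 30%;
- fraction m of those missed, in 2021 only, 25% to 100%;
- the other two NNIS components held fixed.

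Risk with the point: r1 = o/(1 + o), where o = OR × r0/(1 − r0). This gives 0.214 for OR = 2 and 0.290 for OR = 3.

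Risk in the lower stratum in 2021, which now holds the missed patients: low = [(1 − c)·r0 + c·m·r1] / [(1 − c) + c·m].

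Spurious odds ratio, 2021 against earlier, in that stratum: [low/(1 − low)] / [r0/(1 − r0)].

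| c | m | OR | low | spurious odds ratio |
|---|---|---|---|---|
| 0.10 | 0.25 | 2 | 0.1225 | 1.02 |
| 0.20 | 0.50 | 2 | 0.1305 | 1.10 |
| 0.20 | 0.50 | 3 | 0.1389 | 1.18 |
| 0.30 | 0.50 | 3 | 0.1501 | 1.30 |
| 0.30 | 1.00 | 3 | 0.1711 | 1.51 |

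With m = 0 the result is 1.00. Patients correctly left in the upper stratum keep risk r1, so that stratum shows no spurious effect. An estimate pooled over both strata would lie between 1.00 and the tabled value.

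**5. Dilution of wound class as a risk factor.** Within a cohort graded this way, the apparent odds ratio is the true one divided by the factor in step 4. With c = 0.30 and m = 0.50, a true odds ratio of 3 appears as 3/1.295 = 2.32, and one of 2 as 2/1.161 = 1.72.

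**The case against.** A reader might infer that the wound-class input is mis-scored in the 2021 cohort. The document does not say so. Statistical methods ties NNIS scoring to Swissnoso methodology, which is not reproduced, and nothing states that the grade described after Table 1 is the one entered in the index. That description belongs to the risk-factor questionnaire and does not mention NNIS. The sentence is loosely worded, in an article that condenses a fuller protocol.

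A reader might also infer that 2021 was graded differently from the comparators. That is not shown either: neither the grading time in the earlier periods nor the Swissnoso rule is given. With the same timing throughout there is no period-specific error, only a weaker adjustment.

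Nor does the position of the item in the patient-associated column prove pre-operative grading, since length of hospitalization stands in the same column.

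Finally, an under-grading confined to 2021 makes 2021 look worse after adjustment. It would not create a false success for the bundle.

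All of this stands against a claim of demonstrated error. It does not remove the point. The article does not leave the timing open: it states one, for the only wound-class item collected. If the Swissnoso rule counts intraoperative findings, the two sections disagree. If it does not, the adjustment omits contamination that the protocol itself regards as possible.

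**Conclusion.** The concern holds as an inconsistency to be reconciled, with a possible bias. Followed literally, grading before surgery weakens the only named case-mix adjustment and the wound-class risk-factor analysis. If it applies to 2021 alone, the adjusted comparison is biased against the bundle.

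The size cannot be derived from the documents. The range of 1.02 to 1.51 for the spurious odds ratio in the lower stratum rests wholly on the assumptions listed, and its upper end requires every qualifying 2021 patient to be missed. Also, only a change of class that crosses the index's cut-off would alter a patient's score, and the document gives no cut-off. The unadjusted comparison and the Clopper-Pearson interval for the 2021 rate are untouched.

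**What to change.** Replace the timing phrase in the sentence after Table 1 with a statement such as: The wound contamination class used for the NNIS risk index is assigned from the intraoperative findings under the Swissnoso rule, and the same rule applies in all three periods. The sponsor should confirm this against the Swissnoso methodology, because the article does not reproduce it. If that rule sets another time, the text should name it and state the resulting limit of the adjustment.

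Where a 2021 grade was fixed before the operation, check it against the operative report under the rule that produced the comparator data. Re-grading 2021 by a different standard could itself create a difference between periods.

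The cost is one sentence and a check of records. Moving the item to the procedure-associated column of Table 1 is optional labelling.
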